#### Dosing schedule

Both trial treatment arms will follow the same dosing schedule. Eye-drops will be given hourly day and night for 48 hours, then hourly while awake for 5 days, and then 2 hourly while awake for two further weeks. If the ulcer has healed (epithelial defect less than 1 mm, infiltrate resolved, with or without corneal scarring), then treatment is stopped. If resolving stromal infiltration and/or epithelial defect >1 mm but <5 mm, treatment is reduced to four times daily. If resolving but with epithelial defect >5 mm and/or stromal infiltration/hypopyon, treatment is reduced to six times daily. Treatment duration will be tailored to clinical response, with patients reviewed regularly while on treatment in addition to their scheduled study visits.

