### Outcome measures

#### Primary outcome measure

The primary outcome will be BSCVA in logMAR units at 3 months. This will be measured by a trial-certified optometrist, independent of all other aspects of the study and masked to allocation. This has been the primary outcome of several other trials and will therefore facilitate comparison. Three months is the time at which clinical experience suggests most corneal ulcers have usually healed. BSCVA is chosen as it is easy to measure and is of functional significance. We will measure the BSCVA using an LED-backlit, Tumbling-E LogMAR chart (Good-Lite, Illinois, USA) under controlled conditions. We will also measure vision using Peek Acuity, a validated smartphone application, in situations where the patient is unable to attend the hospital for follow-up and outcome data is only available through a domiciliary visit.^29^ For patients who have counting fingers (CF) vision or less, predefined logMAR values will be assigned based on previous clinical trials.^30 31^ Similarly, for patients who undergo a corneal transplant (TPK), a predefined visual acuity of 1.9 logMAR will be given, or last observation carried forward (whichever is the better vision), as per previous studies.^6^

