### Outcome assessments

Participants will be reassessed at 2 days, 1 week, 2 weeks, 3 weeks, 2 months and 3 months following enrolment. Additional examinations, outside the trial protocol schedule may be conducted by the supervising clinician as indicated. The specific assessments to be carried out at each visit are indicated in table 3. These will be conducted in the same way described for the baseline assessment as described (table 2). At each follow-up assessment, the participant will be asked about adherence to treatment and symptoms, including side effects, if still receiving trial treatment. This will be recorded in the case record file. To monitor trial medication adherence, the study participants will be asked to bring their eye-drop bottles to the 1-week, 2-week and 3-week follow-ups. The amount of remaining medication will be measured by weighing the bottle and will be compared with the anticipated remaining amount provided the drops were being used as instructed, resulting in a ratio of actually remaining to what is anticipated. Participants will be resupplied with medication as needed. The presenting visual acuity will be measured on each visit. In addition, the BSCVA will also be measured at the 3-month follow-up (primary outcome measure). At the final 3-month follow-up, the three quality of life questionnaires will be repeated. On each occasion the eyes will be examined using a slit-lamp and the cornea photographed. The IVCM will be repeated at 1, 2 and 3 weeks to determine whether there is evidence of fungal hyphae resolution with the fragmentation of linear elements. At the 1-week follow-up if the ulcer has not healed it will be rescraped for repeat culture to determine whether the keratitis is now culture positive or culture negative. We will give the study participants appointment cards for the next follow-up and they will be reminded about the follow-up a week prior to the date. Public transport costs will be paid for participants who are outpatients.

**Table 3 T3:** Baseline and follow-up assessment components

Assessment item	Baseline	Day 2	Day 7	Day 14	Day 21	Day 60	Day 90
History/baseline questionnaire	X						
Check treatment adherence		X	X	X	X	X	X
Check for side effects		X	X	X	X	X	X
Visual acuity—presenting	X	X	X	X	X	X	X
Visual acuity—BSCVA	X						X
Contrast sensitivity	X						X
Slit-lamp examination	X	X	X	X	X	X	X
Cornea photography	X	X	X	X	X	X	X
In vivo confocal microscopy	X		X	X	X		
Cornea samples (microbiology/PCR)	X		X				

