### Treatment review

At each follow-up visit, participants will be reviewed by an ophthalmic clinician experienced in the management of FK. Clinical responses to antifungal therapy tend to be relatively slow (compared with bacterial infections). Prolonged topical treatment courses of 4–6 weeks are usually needed. Therefore, a change in therapy is usually not made for at least the first week. Other interventions may be indicated such as application of glue to corneal perforations, conjunctival flaps or TPK (corneal transplant).

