#### Secondary outcome analysis

The secondary outcomes outlined above and detailed in table 4 will be analysed by arm. Additional adjustment for factors imbalanced between arms at baseline will be introduced as appropriate. Continuous outcomes will be analysed using linear regression. Binary and ordinal outcomes will analysed using logistic regression. Details of these are given in table 4.

**Table 4 T4:** Secondary outcome measures that will be investigated as part of the trial, together with analysis details

Secondary outcome measure	Details
Three-week BSCVA	We will analyse the secondary outcome of 3 weeks BSCVA in logMAR in the same manner as the primary analysis of the primary outcome described above. The 3 weeks BSCVA will include values taken between 18 days and 5 weeks, with the value closest to 3 weeks used.
Presenting VA by Peek	We will analyse the presenting VA by Peek Acuity with and without pinhole at 3 months as a secondary outcome. This will be of interest if we are unable to get reliable BSCVA measurements at 3 months (ie, if patients fail to attend and we need to attend their houses for visual acuity testing). This will be performed in the same way as the primary analysis of the primary outcome. We will also perform a sensitivity analysis including those lost to follow-up, by using the most recent observation of this variable.
Scar/infiltrate size at 1 week, 3 weeks and 3 months by slit lamp examination	The geometric mean of the two principle axes in mm of the scar or infiltrate at 1 week, 3 weeks and 3 months will be used as a secondary outcome variable. The slit-lamp scar size will be compared at each of these time points between treatment arm in the same manner as described above. This will be by linear regression, with treatment arm and baseline infiltrate/scar size as pre-specified covariates. This controls for the baseline infiltrate/scar size.
Time to full epithelial healing (slit lamp examination by ophthalmic clinician)	Time of re-epithelialisation will be defined as the midpoint between the last review where an epithelial defect (ED) was present and the subsequent review where there was no ED. An area of fluorescein staining of less than 0.5 mm will be considered as a resolved ED due to the difficulty in differentiating a smaller defect from a small amount of fluorescein pooling observed in a healed defect.

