	Analysis of time to healing will use Cox proportional hazards regression with treatment group as the primary predictor and with predictors of baseline ED size (using the geometric mean in mm as outlined above). Survival curves will be plotted using Kaplan-Meier analysis for both treatment arms up to the final visit at 3 months. The proportional hazards assumption will be checked by stratifying on quartiles of the baseline ED size and if the assumption does not hold, the stratified results will be the ones reported. Additionally, treatment failure (defined as persisting epithelial defect greater than 0.5 mm at the 3 month review) will be compared between treatment groups using Fisher’s exact test.
Rate of healing	We will assess how quickly the area of ulceration reduces over time. The rate will be calculated between the 1-week, 3-week and 3-month review by taking the difference in ED size between the two time points, in mm, and diving by the number of days to give a rate of mm/day. Analysis will be performed using Cox regression.
Microbiological cure	Patients who have a persisting corneal ulcer (as defined by the presence of an ED) at day 7 will undergo a repeat corneal scrape and microbiological investigations. Microbiological cure at 7 days will be defined as the absence of any micro-organisms as no significant growth on culture. The number of patients with microbiological cure at day 7 will be compared between the two treatment arms using logistic regression with treatment group and organism (*Aspergillus* spp, *Fusarium* spp, or other) as covariates.
Ulcer depth at 1 week and 3 weeks (slit lamp examination by ophthalmic clinician)	The depth of ulcer in terms of percentage of healthy cornea will be compared at 1 week and 3 weeks between treatment arms, adjusting for baseline depth in the same manner with analysis performed by linear regression
Hypopyon height at 1 and 3 weeks, (slit lamp examination by ophthalmic clinician)	The hypopyon height in mm will be compared at 1 week and 3 weeks between treatment arms, adjusting for baseline hypopyon height in the same manner with analysis performed in the same way (linear regression)

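### Time to epithelial healing is set to an interval midpoint and analysed by Cox regression as if exact; with a 39-day gap between scheduled reviews this can understate a real difference.

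*Protocol article*

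**What the plan says.** In the Protocol article, Table 4 (Secondary outcome analysis) has time of re-epithelialisation "defined as the midpoint between the last review where an epithelial defect (ED) was present and the subsequent review where there was no ED". It continues: "Analysis of time to healing will use Cox proportional hazards regression with treatment group as the primary predictor", with baseline defect size as a further predictor, and "Survival curves will be plotted using Kaplan-Meier analysis for both treatment arms up to the final visit at 3 months". No interval-censored method is named.

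On the visits, Outcome assessments states: "Participants will be reassessed at 2 days, 1 week, 2 weeks, 3 weeks, 2 months and 3 months following enrolment". Table 3 gives the days as 2, 7, 14, 21, 60 and 90. The same section adds: "Additional examinations, outside the trial protocol schedule may be conducted by the supervising clinician as indicated". Dosing schedule describes tailored treatment "with patients reviewed regularly while on treatment in addition to their scheduled study visits". The frequency of these extra reviews is not given, and the endpoint definition does not say whether they count.

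The outcome matters to the trial. Objectives names time to re-epithelialisation among the secondary clinical outcomes, and Table 5 lists it first among the key secondary outcomes.

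**The concern.** What is observed for each eye is a pair of bounds: the last review with a defect and the first without. The midpoint rule discards the bounds and puts one invented time in their place. Where reviews are a week apart little is lost. Between day 21 and day 60 a lot can be, because eyes that closed weeks apart get the same value, and Cox regression reads them as having healed together.

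A substantial share of healing may fall there. The nearest statements in the protocol are indirect: "Prolonged topical treatment courses of 4–6 weeks are usually needed" (days 28 to 42, inside the gap) and "Three months is the time at which clinical experience suggests most corneal ulcers have usually healed".

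At stake is the comparison of healing speed. An estimate pulled towards 1 could hide faster healing on chlorhexidine or, which matters more beside a non-inferiority claim, slower healing.

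**Working it through.** **Inputs from the protocol.** The midpoint rule and Cox model (Table 4) and reviews on days 2, 7, 14, 21, 60 and 90 (Table 3). The protocol gives no event count, hazard ratio or power for this outcome, so there is no figure to reproduce.

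**Assumed, because not given.** Weibull healing times with control median 15, 25, 35 or 45 days and shape 1, 1.5 or 2 (12 scenarios); true HR 1.5; 191 eyes per arm (500 × 0.85 × 0.90 = 382.5, halved); censoring at day 90; 200 replicates per scenario.

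**Step 1: values the rule can give.** On scheduled visits alone: (0+2)/2 = 1, (2+7)/2 = 4.5, (7+14)/2 = 10.5, (14+21)/2 = 17.5, (21+60)/2 = 40.5 and (60+90)/2 = 75. The gap is 60 − 21 = 39 days.

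**Step 2: why the effect shrinks.** Let h be the control cumulative hazard over the gap. Among eyes still open at day 21, the ratio of the proportions closing by day 60 is (1 − e^(−1.5h)) / (1 − e^(−h)), which is below 1.5.
- Median 25, shape 2: h = ln 2 × [(60/25)² − (21/25)²] = 3.50. The ratio is 0.995/0.970 = 1.03.
- Median 45, shape 1: h = ln 2 × 39/45 = 0.60. The ratio is 0.594/0.452 = 1.31.

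The loss is largest when nearly all eyes still open close within the gap. A grouped proportional-hazards model works on the scale where 1.5 is recovered.

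**Step 3: simulation, true HR 1.5, range over the 12 scenarios.**

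| Analysis | Estimated HR | Power |
|---|---|---|
| Cox, exact times | 1.48–1.53 | 94–99% |
| Cox, midpoints, scheduled visits, Efron ties | 1.26–1.51 | 66–97% |
| Same, Breslow ties | 1.19–1.40 | 31–87% |
| Grouped (complementary log-log) model, same visits | 1.48–1.53 | 85–97% |
| Cox, midpoints, about weekly extra reviews to day 49, Efron | 1.47–1.52 | 94–98% |
| Same, Breslow | 1.34–1.48 | 91–96% |

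The share of observed healing that falls between days 21 and 60 is 19–65%, and above half in 5 of the 12 scenarios. In those five the midpoint estimate is 1.26–1.44 (Efron) or 1.19–1.30 (Breslow). With Efron ties, power is within about 2 points of the grouped model in ten scenarios. It is clearly lower in two: 66% against 85% (median 25, shape 2) and 83% against 92% (median 35, shape 2). With Efron ties, then, the main fault is a biased estimate rather than lost power.

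An effect in the other direction shrinks too. With shape 1.5 and medians of 25 and 35 days, a true HR of 0.67 becomes about 0.7 (Efron) or 0.76–0.79 (Breslow).

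**Step 4: medians, shape 1.5, scheduled visits.** Under HR 1.5 the treated median is the control median divided by 1.5^(1/1.5) = 1.310.
- Control 35 days: treated 35/1.310 = 26.7. Both lie in the gap, so both are reported as 40.5, and a true difference of 8.3 days becomes 0.
- Control 25 days: treated 25/1.310 = 19.1. These are reported as 40.5 and 17.5, so a true difference of 5.9 days becomes 23.

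**Step 5: if extra reviews count.** An eye healing on day 30 scores 40.5 on scheduled visits, but (28+35)/2 = 31.5 if seen weekly. The score depends on how often the eye was reviewed. If only 30% of eyes in each arm have weekly extra reviews (shape 1.5, medians 25 and 35), the HR is 1.42–1.44 (Efron) or 1.32–1.33 (Breslow), so part of the attenuation remains.

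**Step 6: no true effect.** On the fixed schedule (shape 1.5, four medians), midpoint estimates are 0.99–1.01 and rejection is 0–4%.

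**The case against.** The best defence is that the 39-day interval may seldom arise. The definition speaks of a review, not a scheduled visit. Patients on treatment are seen in addition to the schedule, and an eye with an open defect would normally still be on treatment. With about weekly reviews and Efron ties the attenuation nearly disappears. This stands as a limit on the size of the problem. It does not remove it, because the protocol fixes neither the frequency of those reviews nor whether they count. Nor does being on treatment guarantee cover up to the endpoint: Dosing schedule treats a defect under 1 mm with resolved infiltrate as healed, whereas Table 4 counts healing only below 0.5 mm.

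Second, the lowest estimates need Breslow ties and attendance on the exact day. Tie handling is ordinarily left to the analysis plan, and real visits scatter. With assumed scatter of 1–3 days up to day 21 and 7 days at days 60 and 90 (shape 1.5, medians 25 and 35, 40 replicates), estimates were 1.39–1.44 (Efron) and 1.37–1.42 (Breslow). This stands: the Breslow figures are a worst case, but modest attenuation remains.

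Third, Fisher's exact test of persisting defect at 3 months needs no midpoint. True, but it compares whether eyes healed, not how fast, and speed is the stated objective.

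**Conclusion.** The point holds in a limited form. If scheduled visits alone count, a true HR of 1.5 is estimated at about 1.26–1.51 with Efron ties, and lower with Breslow ties on exact visit days; medians that lie in the gap are all reported as day 40.5. If the extra reviews count and are about weekly, the HR is nearly right, but midpoints and medians depend on review frequency. These are alternative readings of the rule, and their effects should not be added. All sizes rest on assumed Weibull healing times.

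Three stronger readings are not supported:
- A reader might infer that healing usually falls in the gap. The 4–6 weeks is treatment duration, which also waits for the infiltrate to resolve, so the epithelium may close earlier. The share was above half in only 5 of 12 assumed scenarios.
- A reader might infer that any treatment effect must be attenuated. With frequent reviews it largely is not.
- A reader might infer a false difference between arms from unequal reviewing. An 8-day shift in medians (29.2 against 37.5) can be produced with no true effect, but only by assuming weekly extra reviews in 50% of eyes in one arm and 20% in the other. The arms share one schedule and the assessing clinicians are masked. Even then the HR moves only to 1.02 (Efron) or 1.06–1.08 (Breslow).

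The false-positive rate on the fixed schedule is not inflated, and the primary non-inferiority conclusion is unaffected.

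**What to change.** Keep each eye's two bounds (last review with a defect, first review without) and analyse them with an interval-censored proportional-hazards model. Alternatively, fit a complementary log-log model on the scheduled visit intervals. Adjust for baseline defect size as already planned. Replace the midpoint Kaplan-Meier curves and medians with Turnbull curves or with proportions healed at scheduled visits. State whether unscheduled reviews count: the interval-censored model can use them through the true bounds, while the complementary log-log model should use scheduled visits only.

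The cost is a change of analysis wording and slightly more analysis work with standard software. No visit or measurement is added. The one loss is that the median may be reportable only as an interval.

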#### Non-pharmacological treatment

It is sometimes necessary to perform surgical procedures during the management of corneal infections. In the context of the trial these will be performed by the supervising consultant ophthalmologist. These can include:

Insertion of a bandage contact lens for very small perforations.Tissue glue and patch for small perforations.Corneal transplant (TPK) for progressive fungal infections that are refractory to medical management or large perforations.Conjunctival flaps to cover corneas in non-healing ulcers.

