Perforation and/or TPK and/or conjunctival advancement by 3 months (slit lamp examination by ophthalmic clinician)	The number of patients who undergo perforation and/or require TPK and/or have undergone conjunctival advancement by 3 months will be reported using CIs and descriptive statistics. The study is not powered to detect a difference in perforation rate or TPK between treatment groups; not reporting a significant difference may be wrongly interpreted as there being no difference between groups. We will therefore perform an exploratory analysis to compare TPK or perforation rates between treatment groups. This will be by logistic regression to compute an OR by arm.
Loss of eye	The number of patients who have their eye surgically removed (evisceration or enucleation) during the 3 months follow-up period will be reported using CIs and descriptive statistics in the same way as for TPK/perforation rate above, along with exploratory analysis using logistic regression to find risk factors for eye loss and OR for this by arm.
Ocular adverse effects, slit lamp examination by ophthalmic clinician	The proportion of patients with one or more adverse events will be compared using Fisher’s exact test. Additional analysis to compare the rate of adverse events during the 3 months follow-up will be by Poisson regression as this can take into account multiple instances within one participant.
QoL assessed using: EQ-5D, WHO/PBD-VF20, WHOQOL-BREF	QoL can be assessed quantitatively using different tools depending on what is of interest. For example, disease-related QoL can be assessed (eg, vision related QoL, VRQoL) or more general health-related issues irrespective of the disease can be investigated (health-related QoL, HRQoL).^40^
	We will use the WHO/PBD-VF20 (WHO/ Prevention of Blindness and Deafness—Visual Functioning 20-item questionnaire) VRQoL tool. This tool measures the impact of visual impairment in the person’s life including mental well-being, dependency and social functioning. These have been used in a number of other visual related studies to show a difference in QoL.^36 37^

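### Treatment failure and time to healing take no account of corneal transplant, conjunctival flap or eye removal, so eyes in which medical treatment failed can be scored as non-failures, and grafted or flapped eyes as healed

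*Protocol article*

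**What the plan says.** All of this is in the protocol article.

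- **Healing.** In Table 4, row on time to full epithelial healing, re-epithelialisation is dated as "the midpoint between the last review where an epithelial defect (ED) was present and the subsequent review where there was no ED". A small residual area is disregarded: "An area of fluorescein staining of less than 0.5 mm will be considered as a resolved ED".
- **Model.** "Analysis of time to healing will use Cox proportional hazards regression with treatment group as the primary predictor", with baseline defect size as a further predictor. "The proportional hazards assumption will be checked by stratifying on quartiles of the baseline ED size".
- **Failure.** The same row adds a Fisher comparison of "treatment failure (defined as persisting epithelial defect greater than 0.5 mm at the 3 month review").
- **Surgery.** The section on non-pharmacological treatment lists "Corneal transplant (TPK) for progressive fungal infections that are refractory to medical management or large perforations" and "Conjunctival flaps to cover corneas in non-healing ulcers".
- **Where surgery is counted.** Table 4 has one row for perforation, TPK or conjunctival advancement, and another for eye loss: "The number of patients who have their eye surgically removed (evisceration or enucleation) during the 3 months follow-up period". Both are reported descriptively, with exploratory logistic regression by arm.
- **Primary outcome.** That section has a rule for TPK: 1.9 logMAR or the last observation carried forward, whichever is the better vision. The healing row has no counterpart.

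**The concern.** Both rules look only at whether a defect is visible at a review. They do not ask how the surface came to be intact. TPK removes the ulcerated cornea and a flap covers it, so either can end the defect without any healing under the trial drug. Very severe ulcers warranting an immediate conjunctival flap or evisceration are excluded at entry, so a flap or an evisceration in the trial generally follows trial treatment and speaks to its result.

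If such eyes count as non-failures, the comparison labelled treatment failure leaves out patients in whom treatment most plainly failed. If they also receive a healing time, an operation for non-healing becomes a healing event. Both errors favour the arm with more surgery. Time to full epithelial healing is among the key secondary outcomes in Table 5, so the definition matters to how the result will be read.

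**Working it through.** The article states no figure for failure or healing, so there is none to reproduce. The check applies the written rules to each type of eye and then works an illustration.

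**1. The rules applied literally**

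| Course of the eye | Failure at 3 months? | Healing time? |
|---|---|---|
| Defect >0.5 mm persists, no surgery | Yes | No |
| TPK, graft surface intact at the next review and at 3 months | No | Yes, if a defect was present at the last review before surgery |
| TPK, graft has its own defect >0.5 mm at 3 months | Yes, through the graft surface | Only if an intermediate review showed no defect |
| Flap covering a non-healing ulcer, no defect seen afterwards | No | Yes, on the same condition |
| Evisceration or enucleation | Cannot meet the definition | Not stated |

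**2. Effect on dating**

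Reviews fall on days 2, 7, 14, 21, 60 and 90. Take an eye with a defect on day 21, grafted afterwards, with an intact graft on day 60. Its healing time is (21 + 60)/2 = day 40.5. An eye that heals slowly on the drug, with a defect on day 60 and none on day 90, is dated (60 + 90)/2 = day 75. The grafted eye is recorded as the faster healer.

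**3. Effect on the failure comparison (illustration)**

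Inputs from the document: 500 randomised and 15% drop-out, so 250 × 0.85 = 212.5, taken as 212 per arm.

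Assumptions, none of them in the document:
- TPK, flap or eye removal in 25% of the natamycin arm and 15% of the chlorhexidine arm.
- No qualifying defect at 3 months in those eyes.
- A persisting defect in a share e of the remaining eyes, the same in both arms.

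With s the surgery rate, failure as written is e(1 − s), and failure including surgery is s + e(1 − s).

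At e = 5%:
- As written: 0.05 × 0.75 = 3.75% v 0.05 × 0.85 = 4.25%, or 8 v 9 eyes, Fisher p = 1.00.
- Surgery counted: 25% + 3.75% = 28.75% v 15% + 4.25% = 19.25%, or 61 v 41 eyes, p = 0.031.

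| e | As written | p | Surgery counted | p |
|---|---|---|---|---|
| 3% | 2.25% v 2.55% | 1.00 | 27.25% v 17.55% | 0.020 |
| 5% | 3.75% v 4.25% | 1.00 | 28.75% v 19.25% | 0.031 |
| 10% | 7.50% v 8.50% | 0.86 | 32.50% v 23.50% | 0.051 |

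Swapping the two surgery rates mirrors every row. As written, the arm with more surgery always has slightly fewer failures, but the difference is trivial. The main effect is that a real contrast disappears from the comparison. With equal surgery rates both versions show no difference.

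**4. Surgery tested alone**

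On the same assumptions, 53/212 v 32/212 gives Fisher p = 0.015. An analysis of the kind already planned for the surgical row would therefore show the contrast without any change to the failure definition.

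**The case against.** The strongest reply is that nothing is lost to the trial. TPK and perforation are compared by arm, conjunctival advancement is reported in the same row, and eye loss has its own odds ratio. The primary outcome has its TPK rule, and sensitivity analyses address TPK and perforation. A reader of the full report would see an arm with more surgery, and step 4 bears this out. That stands, and it limits the harm. It does not correct the Fisher test or the Cox model, whose results will be read under the names failure and healing.

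A second reply is that censoring and competing-event rules are commonly left to an analysis plan, which is not shown. That holds for an unstated rule. The failure criterion, however, is stated in full, as is the dating of healing, and both give a definite answer for an intact graft or flap. A plan could narrow re-epithelialisation to the presenting defect, but the article does not. Censoring at surgery would not be neutral either, because surgery marks eyes that were not healing.

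Three stronger readings are tempting, and the document does not support them:
- A reader might infer that removed eyes are counted as healed. They have no cornea to assess, and the article does not say whether they are non-failures, missing or censored.
- A reader might take the quoted quarter of cases, about 125 of 500, as the number misclassified. That figure is for perforation and loss of the eye, not for graft or flap. Small perforations may be managed with a bandage lens or glue, and those eyes can truly re-epithelialise.
- A reader might infer that the failure comparison would favour the arm with more surgery by a material amount. In the illustration the reversal is half a percentage point.

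**Conclusion.** The point holds for the two definitions. As written, the failure criterion passes over eyes with an intact graft or flap, and the healing rule can date them as healed, although the protocol describes these operations as used for refractory or non-healing disease. Removed eyes cannot meet the failure criterion, and their handling is unstated. The harm is limited to the failure comparison, which is an additional test within one Table 4 row, and to the secondary time-to-healing outcome. The primary non-inferiority analysis is not touched.

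The size is not known, because the document gives no 3-month rates of TPK, flap or eye removal. The illustration shows only what could happen under assumed rates that differ between arms. The change should be made, but the trial's main conclusion does not depend on it.

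A minor and separate point: stratifying on quartiles of baseline defect size examines a covariate. It does not test whether the treatment hazard ratio, which is the reported effect, is constant over time.

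**What to change.** 1. **Failure comparison.** Define treatment failure as a persisting epithelial defect greater than 0.5 mm at the 3-month review, or TPK, conjunctival flap or advancement, or evisceration or enucleation before that review. Keep Fisher's test.
2. **Time to healing.** State that a defect-free review after any of these procedures is not healing. Treat the eye as not healed through day 90, either as a competing event with cumulative incidence curves or by keeping it in the risk set to day 90. Either is acceptable if fixed before unmasking.
3. **Proportional hazards.** Add a check for the treatment term, for example with Schoenfeld residuals or a treatment-by-time term.

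The cost is wording and slightly more analysis work, because the surgical events are already recorded for other Table 4 rows. The revised failure outcome will overlap with the surgical row, and the report should say so. No change to clinical management is involved.

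### Three-month treatment failure is compared by an unadjusted Fisher's exact test, although the plan's general rule is logistic regression and the same table row already uses baseline defect size as a covariate

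*Protocol article*

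**What the plan says.** All places are in the protocol article, section Secondary outcome analysis, including its Table 4.

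- General rule: "Binary and ordinal outcomes will analysed using logistic regression". The text adds "Additional adjustment for factors imbalanced between arms at baseline will be introduced as appropriate" and refers the reader to Table 4 for details.
- Table 4, row on time to full epithelial healing: the time-to-event analysis is a Cox model "with treatment group as the primary predictor and with predictors of baseline ED size". Treatment failure, defined as a defect above 0.5 mm persisting to the last visit, is an additional binary comparison that "at the 3 month review) will be compared between treatment groups using Fisher’s exact test". No covariate and no effect measure is named for it.
- Table 4, row on ocular adverse effects: "The proportion of patients with one or more adverse events will be compared using Fisher’s exact test". The row continues: "Additional analysis to compare the rate of adverse events during the 3 months follow-up will be by Poisson regression".
- Table 4, rows on microbiological cure, perforation/TPK and loss of eye: these binary outcomes do follow the general rule. For perforation/TPK the wording is "This will be by logistic regression to compute an OR by arm".

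**The concern.** The general sentence and the treatment-failure row name different analyses for the same outcome, and no reason is given for the departure. The choice has three consequences.

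- Fisher's test conditions on the total number of events, so its actual size is below the nominal level. Some power is lost for no gain beyond exactness, which matters only when events are sparse.
- It takes no covariates. Baseline defect size is plausibly prognostic for a defect that persists at three months, and the plan already treats it that way in the Cox model of the same row. The promised adjustment for imbalanced baseline factors cannot be made either.
- As written, the comparison yields a p-value only. For perforation the plan itself cautions that "not reporting a significant difference may be wrongly interpreted as there being no difference between groups". That remark concerns a different outcome, but the reasoning carries over to any low-powered binary comparison.

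At stake is the precision and interpretability of a secondary efficacy comparison.

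**Working it through.** **Inputs from the protocol article.** Recruitment target 500, drop-out 15%, SD 0.5, margin 0.15 logMAR, power 90%, alpha 0.0492 (Sample size considerations); 1:1 allocation (Sequence generation).

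**Assumptions.** The article gives no failure rate, no adverse-event rate and no prognostic strength for defect size. I assume event rates of 5% to 30%, a nominal two-sided 5% level for secondary tests, and baseline defect size as a standard normal covariate with an odds ratio of 1, 2 or 3 per SD.

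**Step 1: number per arm.** There is no stated figure for these comparisons to reproduce. The nearest is the primary sample size, used here only to fix the evaluable number. With alpha 0.0492 taken one-sided, n per arm = 2 × 0.5² × (1.653 + 1.282)² / 0.15² ≈ 191.4, rounded up to 192. Then 2 × 192 = 384, and 384 / 0.85 = 451.8, which gives the stated 452. For the secondary outcomes I use 500 × 0.85 = 425, or about 212 per arm. The range checked is 192 (from 384) to 225 (500 × 0.90 / 2).

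**Step 2: actual size of Fisher's test.** Size(p) = Σ over x, y of Bin(x; n, p) × Bin(y; n, p) × I[Fisher p-value (x, y) ≤ 0.05], by full enumeration.

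| Common event rate | Fisher, 192 / 212 / 225 per arm | Arm-only logistic score test, 212 per arm |
|---|---|---|
| 5% | 2.8 / 3.0 / 3.1% | 4.8% |
| 10% | 3.3 / 3.5 / 3.5% | 4.9% |
| 15% | 3.5 / 3.7 / 3.7% | 5.0% |
| 20% | 3.7 / 3.8 / 3.8% | 5.0% |
| 30% | 3.9 / 3.9 / 4.0% | 5.0% |

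**Step 3: power without a covariate, 212 per arm, exact.**

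- 5% v 12%: Fisher 69.2%, logistic score test 74.5%, gain 5.3 points.
- 10% v 20%: 79.7% and 83.1%, gain 3.4 points.
- 20% v 30%: 62.5% and 66.7%, gain 4.2 points.

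**Step 4: power with baseline defect size in the model.** Likelihood-ratio test for arm, 212 per arm, 6,000 simulated trials per scenario (simulation error about 0.6 points or less), arm-level event rates held at the stated values. The comparator is the exact Fisher power.

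| Failure rates | Fisher | Adjusted, OR 1 per SD | OR 2 per SD | OR 3 per SD |
|---|---|---|---|---|
| 8% v 16% | 67.9% | 73.2% | 74.5% | 78.2% |
| 10% v 20% | 79.7% | 84.0% | 85.8% | 88.0% |

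The largest gain is 78.2 − 67.9 = 10.3 points. The smallest across steps 3 and 4 is 3.4.

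**Step 5: type I error of the adjusted test.** At 10% in both arms it rejects in 4.9% to 5.2% of trials. At 5% in both arms it rejects in 5.4% to 5.9%, slightly liberal.

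**Step 6: where the alternative fails.** At a 1% event rate and 212 per arm, arm-only logistic regression has actual size of about 9.6% by likelihood ratio and 0.1% by Wald. The score test stays near 4%. A rule for sparse data is therefore needed.

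**The case against.** The strongest reply is that there is no true contradiction. The general sentence is a default, it points to Table 4 for details, and Table 4 departs from the defaults elsewhere too, for example with t-tests for costs. That reading is reasonable. The table does not say that it overrides the text, however, so alignment is still worthwhile.

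Second, both rows already carry an effect estimate: an adjusted hazard ratio for time to healing, and a Poisson rate ratio for adverse events. This stands and limits the loss. Neither is an estimate for the binary outcome itself. A confidence interval for a supplementary comparison may also simply be left to a fuller document, so its absence alone is not the point.

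Third, Fisher's test is valid, every event rate above is assumed, and part of the power gain is only the recovery of unused alpha. All true. In step 3 the whole gain of 3 to 5 points comes from that source. What goes beyond it in step 4 depends on how prognostic defect size is.

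A reader might infer that a conservative, p-value-only test on failure and harm tilts a non-inferiority trial towards chlorhexidine. The documents do not support this. Non-inferiority is judged on three-month visual acuity alone, no such claim is attached to failure or adverse events, and a two-sided test hides a difference in either direction equally. A reader might also extend the covariate argument to adverse events. That row has no baseline-defect adjustment, and nothing in the article calls for one.

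**Conclusion.** The point holds as a modest, cost-free improvement. For treatment failure, Fisher's test departs from the plan's general rule, runs at about 3.0% to 3.9% instead of 5% for event rates of 5% to 30% with 212 per arm, and discards a covariate that the same row already uses. Adjusted logistic regression adds roughly 3 to 10 points of power under the assumed rates. The upper end needs an odds ratio near 3 per SD of baseline defect size. Type I error stays near nominal at a 10% rate, and the method should not be used when events are very sparse. For adverse events, only the wording and the missing risk difference are at issue. Fisher's test does not inflate type I error, and the primary analysis is untouched.

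**What to change.** - **Treatment failure.** In the Table 4 row, replace Fisher's test by logistic regression on arm and baseline epithelial defect size. Report the odds ratio with a 95% CI. If an absolute measure is wanted, add a risk difference standardised over the observed baseline defect sizes, with its CI.
- **Sparse events.** Fix in advance, on the total across arms and before allocation is revealed, the event count below which Fisher's test is used instead. A count near 20 would match the lowest rate checked in step 5 (424 × 5% ≈ 21).
- **Adverse-event proportion.** Keep Fisher's p-value if preferred, and give the risk difference with a 95% CI beside it.
- **General sentence.** State that logistic regression applies unless Table 4 specifies otherwise, so that text and table agree.

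The cost is wording in the analysis plan. Epithelial defect size is already measured at the baseline slit-lamp examination, so no new data, visits or patients are needed.
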